### 3 OBJECTIVES

#### 3.1 Primary objectives

To perform a study to:

1. Estimate the prevalence of elevated albuminuria in subjects with a high risk of chronic kidney disease in the Netherlands.
2. Evaluate which screening approach would be most effective based on costs per identified patient with elevated albuminuria, via pharmacies or general practices.

#### 3.2 Secondary objectives

1. To estimate the prevalence of unrecognized chronic kidney disease in subjects with a high risk of chronic kidney disease in the Netherlands.
2. To estimate the prevalence of persistent elevated albuminuria under adequate treatment with renin-angiotensin system (RAS) inhibitors in subjects with a high risk of chronic kidney disease in the Netherlands
3. To assess frequency of cardiovascular risk monitoring by general practitioners after targeted albuminuria screening.
4. To assess changes in cardio-metabolic drug prescriptions after targeted screening.

### 4 STUDY DESIGN

The SALINE study is a cross-sectional study that consists of two phases: *a targeted screening phase*, and (only if elevated albuminuria is confirmed) an *elaborated screening phase*. An overview of the study design is shown in Figure 2.

Potential participants will be recruited via:

1. Pharmacies through database selection on prescribed medication for Diabetes Mellitus, hypertension or lipid disorders.
2. General practices through a history of Diabetes Mellitus, hypertension, cardiovascular disease, lipid disorders and/or obesity in patient electronic medical records using VIPlive.

[figure not shown]

Figure 2. Overview of the study design

In the pilot study, 2 pharmacies and 3 general practitioners were included. For the extension, 3 pharmacies and 7 general practitioners will be recruited.

We assume that at least 6300 patients from general practices and pharmacies will be eligible for inclusion in the screening phase. We aim to examine at least 112 patients with elevated albuminuria at the elaborated screening phase in this study. In the pilot study, 57 patients were examined at the elaborated screening phase.

The effectiveness of both screening approaches in finding elevated albuminuria will be evaluated by calculating the total screening costs per identified patient with elevated albuminuria and compared. An amendment to the protocol may be proposed for ethical approval to extent screening to a larger population based on the results.

#### 4.1 Phase 1: Targeted screening on albuminuria

##### Targeted screening via pharmacies

Pharmacies will select eligible subjects to be invited for albuminuria screening from their database, based on delivered medication that has an indication for hypertension, Diabetes Mellitus, or lipid disorders in the last 6 months, based on combined information on ATC codes (chapter 4.2.1) for prescribed medication and available registered information on subjects having these indications.

#### Targeted screening via general practitioners

General practitioners will select eligible subjects for albuminuria screening from subjects' electronic medical records, based on the presence of risk factors for elevated chronic kidney disease. Using a VIPlive selection report, subjects will be selected based on recording of one or more of the following:

3. An ICPC code for Diabetes Mellitus
4. An ICPC code for cardiovascular disease, including hypertension
5. An ICPC code for lipid disorders
6. An ICPC code for obesity or a calculated BMI  $\geq 30$  kg/m^2, based on height and weight

If albuminuria status was recently (within 18 months) assessed by the general practice and was found to be 'normal' (< 3.0 mg/mmol), subjects will not be invited for albuminuria screening. All other subjects with an increased risk of chronic kidney disease will be invited by their general practice to participate.

#### Potential overlap

Potential overlap in subject recruitment occurring when participating pharmacies are providing services to subjects of also participating general practitioners will be avoided as much as possible. In case of known overlap at the recruitment phase, data available from the general practitioner will be preferred. All subjects being registered as a patient from a participating GP in the pharmacy database will be excluded from the selection list from the pharmacy.

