## 9 METHODS

### 9.1 Study endpoints

#### 9.1.1 Primary endpoints

1. Elevated albuminuria, defined as a urinary albumin creatinine ratio (UACR)  $\geq 3.0$  mg/mmol.
2. Average screening costs per subject that was identified as having kidney disease by screening for albuminuria. All costs considered are mentioned below (Table 1)

Table 1. Costs associated with screening

|                                                                             |
|-----------------------------------------------------------------------------|
| Costs of the PeeSpot                                                        |
| Laboratory costs                                                            |
| Printing and postal mailing costs of all invitations and needed information |
| Labor costs needed to recruit and start GP's and pharmacies                 |
| Labor costs of training GP's and pharmacies                                 |
| Costs of extracting patients eligible for inclusion                         |

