## **11 STATISTICAL ANALYSIS**

Characteristics of subjects recruited will be described as mean values with standard deviation or median with interquartile range for continuous variables. Categorical variables will be described as numbers and percentages of the subjects per category.

The overall prevalence of elevated albuminuria, and prevalences of unrecognized and persistent elevated albuminuria despite a RAS-inhibitor are described as percentages with 95% confidence intervals. The number of eligible patients from general practices who fulfilled the inclusion criteria but had an albuminuria level  $<3$  mg/mmol recorded within 18 months prior to selection (and where therefore not invited to participate), will be included in the denominator to calculate the prevalences.

To compare effectiveness and costs of screening on elevated albuminuria in pharmacies and in GP-care, the costs for the targeted screening strategies in both pharmacies and GPs will be calculated.

For each approach, all costs associated with the screening will be added and divided by the total number of subjects identified with confirmed elevated albuminuria. A screening-

approach will be considered more effective than the other if the costs per identified patient are  $\geq 10\%$  lower.

Frequencies of cardiovascular monitoring and treatment changes are summarized as numbers and percentages with 95% confidence intervals.

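### Removing participating GPs' patients from the pharmacy list, with pharmacy site costs left whole, can raise pharmacy cost per case; removals should be counted and a cost-apportioned figure reported

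*Protocol*

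**What the plan says.** Primary objective 2 (Protocol section 3.1) is to "Evaluate which screening approach would be most effective based on costs per identified patient with elevated albuminuria, via pharmacies or general practices".

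Under the Potential overlap heading in section 4.1, the protocol says that overlap between participating pharmacies and participating practices "will be avoided as much as possible". It then settles what remains: "In case of known overlap at the recruitment phase, data available from the general practitioner will be preferred", and "All subjects being registered as a patient from a participating GP in the pharmacy database will be excluded from the selection list from the pharmacy". No matching removal from the GP list is described.

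Table 1 in section 9.1.1 lists the costs that count. Three items attach mainly to the site: "Labor costs needed to recruit and start GP's and pharmacies", "Labor costs of training GP's and pharmacies" and "Costs of extracting patients eligible for inclusion". The others (PeeSpot, laboratory, printing and postage) follow the number of people invited or tested.

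Section 11 gives the estimator. Within each route, "all costs associated with the screening will be added and divided by the total number of subjects identified with confirmed elevated albuminuria". Either route is called more effective if its cost per identified patient is at least 10% lower. No apportionment for patients struck from the pharmacy list is mentioned, and no count of them is asked for.

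**The concern.** A pharmacy that loses part of its list to the overlap rule still has to be recruited, started and trained, and its database still has to be searched. The cases it might have found among the removed patients leave the denominator, while those costs stay in the numerator. The GP route loses nobody to the pharmacy.

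A pharmacy programme run on its own would have no reason to strike these patients, so the removal comes from running both routes side by side. The Summary says the study will guide larger programmes, and section 4 foresees an amendment to extend screening on the basis of the results. For those decisions the relevant quantity is the cost per case of each route by itself.

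Section 11 already corrects the prevalence denominator for GP patients who were not invited because of a recent normal result. The cost endpoint has no comparable correction for pharmacy patients left out by a study rule. At stake is a primary comparison decided by a fixed 10% margin.

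**Working it through.** The protocol states no cost, overlap or cost-per-case figure, so there is nothing to reproduce. The check is algebraic.

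**Inputs from the protocol:** one-way removal (section 4.1); cost items (Table 1); total cost divided by confirmed cases, and the 10% rule (section 11).

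**Assumed, not in the protocol:** F = fixed pharmacy site costs; v = cost per invited patient; N = full pharmacy list; p = confirmed cases per invitation, the same in removed and retained patients; o = share of the list removed. The fixed-cost share is f = F/(F + vN).

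**Inflation factor**

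- Full list: (F + vN)/(Np).
- After removal: (F + vN(1−o))/(N(1−o)p).
- Ratio of second to first: (1−f) + f/(1−o) = 1 + f·o/(1−o).

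| f | o = 10% | o = 20% | o = 30% |
|---|---|---|---|
| 10% | 1.011 | 1.025 | 1.043 |
| 20% | 1.022 | 1.050 | 1.086 |
| 30% | 1.033 | 1.075 | 1.129 |
| 50% | 1.056 | 1.125 | 1.214 |

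**Overlap needed to meet the 10% rule from true parity.** At least 10% lower means GP/pharmacy ≤ 0.9, so pharmacy/GP ≥ 1/0.9 = 1.111. Setting f·o/(1−o) = 0.111 gives o = 0.111/(f + 0.111):

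- f = 20%: 0.111/0.311 = 36%
- f = 30%: 0.111/0.411 = 27%
- f = 40%: 0.111/0.511 = 22%

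**Near the threshold.** At f = 30%, o = 20%, the observed GP/pharmacy ratio is the true ratio divided by 1.075. GP is declared more effective once the true ratio is at or below 0.9 × 1.075 = 0.9675, a true advantage of about 3%. In the other direction, the pharmacy route would need a true pharmacy/GP ratio of 0.9/1.075 = 0.837 or lower, about 16% cheaper, to be declared more effective.

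**Dependence on equal yield.** If yields differ, the factor becomes [1 + f·o/(1−o)] × (full-list yield / retained yield). At f = 30%, o = 20% it cancels when retained yield is 1.075 times the full-list yield. The removed patients' yield would then be (1 − 0.8 × 1.075)/0.2 = 0.70 of the full-list yield, or 0.70/1.075 = 0.65 of the retained yield.

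**Check of the apportioned figure.** Take illustrative values F = 3000, v = 7, N = 1000, so f = 30%, with p = 0.0178 and o = 20%. The value of p is 112/6300 from section 5.4; it cancels in the ratios.

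- Full list: 10000/17.8 = 561.8 per case.
- After removal: 8600/14.24 = 603.9, ratio 1.075.
- With F multiplied by the retained share, 0.8: (2400 + 5600)/14.24 = 561.8, ratio 1.000.

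**The case against.** The strongest reply is that the effect may be negligible. The protocol's first instruction is to avoid overlap, and list removal deals only with what is left. Nothing in the protocol suggests overlap of 20–35%, and if sites have separate catchments the factor is exactly 1. Sampling error may also be larger: if 112 confirmed cases split evenly between routes (an assumption), Poisson error alone puts the 95% range of the cost-per-case ratio at about a factor of exp(1.96 × √(2/56)) = 1.45 either way. This stands as a limit on size. It does not remove the point, because no method or ceiling for avoiding overlap is given, and without a count nobody can show afterwards that it was small.

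The rule also has practical grounds. Section 4.1 assumes that the pharmacy database shows the patient's GP, and GP records hold the albuminuria results used for the 18-month exclusion and the 11-month waiver of confirmation. Avoiding double invitation is sound and need not change.

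Table 1 does not say which items are independent of list size. Section 12.5 reimburses sites according to time spent, so some labour, extraction included, may scale with the list. That lowers f but does not make it zero.

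A supplementary cost analysis could sit in a statistical analysis plan. The count of removals, however, has to be taken when the lists are drawn, and the protocol fixes both the removal rule and the cost formula.

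A reader might infer that the bias always runs against the pharmacy route. It does so only if removed and retained patients have similar yield; a sufficiently low yield among those removed would cancel or reverse it.

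**Conclusion.** The point holds as a modest weakness that is cheap to repair. One-way removal combined with unapportioned site costs raises pharmacy cost per case by 1 + f·o/(1−o), given some overlap, some fixed cost and equal yield. Since f and o are not in the protocol, the actual size cannot be established from it.

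A reader might go further and infer that the study would favour general practice because of its own overlap rule, or that 10% inflation is enough to trigger the decision. The protocol supports neither. The rule requires a ratio of 1.111, so f = 40% with o = 20% (1.10) falls just short, and from parity the overlap would have to be substantial. Smaller overlap changes the conclusion only when the true ratio already lies near a threshold.

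**What to change.** 1. Keep the single-invitation rule in section 4.1.
2. Have each pharmacy record the number of otherwise eligible subjects removed for overlap. For the two pilot pharmacies, retrieve this where possible.
3. In section 11, report beside the unadjusted pharmacy cost per case a second figure with fixed site costs multiplied by invited/(invited + removed). Name the Table 1 items treated as fixed.
4. State whether the 10% conclusion is the same under both figures.

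The cost is one count per pharmacy and one extra line in the cost calculation. Section 11 already asks pharmacies for data used in selecting subjects. The adjusted figure assumes that removed patients would have responded and tested like those invited, and pilot counts may be unavailable; both limits should be reported.

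Splitting overlapping patients at random between routes is not a good substitute. At f = 30%, o = 30%, half the overlap (15%) would still leave the pharmacy list, for a factor of 1 + 0.3 × 0.15/0.85 = 1.053, and the GP route would become inflated too.

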#### Albuminuria screening using PeeSpot

Selected subjects will receive an invitation to participate in the screening survey from their pharmacy or general practice by postal mail, including an informational letter about the study, an informed consent form, a short questionnaire to be completed (Appendix 16.1)

and a urine collection device (PeeSpot) with instructions. The participant will be asked to send the signed informed consent form and completed questionnaire and the collected urine to the General Practitioners Research Institute (GPRI) by postal mail (without costs). If the laboratory measures 'normal' albuminuria ( $<3.0$  mg/mmol), GPRI will inform the subject. In case of elevated albuminuria ( $\geq 3.0$  mg/mmol), GPRI will be informed to send a second PeeSpot for a confirmational measurement if informed consent has been received. If this second measurement is also elevated ( $\geq 3.0$  mg/mmol), subjects will be invited for an elaborated screening visit performed by GPRI (phase 2). A second confirmational measurement of elevated albuminuria will not be required when a recent (within 11 months) measurement performed by the general practice also indicated elevated albuminuria.

#### **4.2 Phase 2: Elaborated screening phase**

When there is no elevated albuminuria at phase 1, a letter with the results will be sent to the participant, and no further actions from the participant are required. Subjects will be carefully informed about the results.

When elevated albuminuria is confirmed ( $\geq 3.0$  mg/mmol on two occasions), subjects are invited for an elaborated screening visit with a researcher. At the start of the visit, participants will be asked to provide informed consent. Next, CKD/CVD risk factors will be assessed and the participant's medication use, and medication adherence will be reviewed during an interview. GPRI will produce a report of their findings which will be shared with the general practice, including recommendations for additional measurements or treatment changes if applicable.

#### **4.3 Phase 3: Implementation of care**

In phase 3 of the SALINE study we will determine if cardiovascular risk factor monitoring and cardiometabolic drug prescriptions changes within 6 months after participants have participated in the screening phases of the study. To this end, data about cardio-metabolic risk factor monitoring and prescriptions will be extracted from the database of the general practitioner and/or pharmacies involving all patients who qualified for the SALINE study (thus both those who participate in SALINE and those who did not). We will then determine

the frequency of cardio-metabolic risk factor monitoring and if drug prescriptions have occurred in the 6 months following the albuminuria targeted screening and compare those with participants who did not participate in SALINE.

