#### 9.1.2 Secondary endpoints

1. Unrecognized chronic kidney disease, defined as elevated albuminuria, not reported by the subject and not previously recorded in electronic medical records of the subjects' general practice or pharmacy.
2. Persistent elevated albuminuria, defined as elevated albuminuria persisting despite good adherence to treatment with RAS-inhibitors for at least 6 weeks prior to elevated albuminuria assessment (score  $\geq 4$  on the Medical Adherence Report Scale (MARS)) (Appendix C, paragraph 16.3).
3. Change in frequency of cardiovascular risk factor monitoring, defined as the difference between the frequency of cardiovascular risk factor monitoring in participants 3 years before and 6 months after targeted albuminuria screening.
4. Changes in cardiometabolic drug prescriptions, defined as changes in any prescription for cardiovascular disease or CKD 6 months after targeted albuminuria screening compared to three years before.

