#### Implementation of care

After the study visits have been completed, data extractions from the general practitioners and/or pharmacies will be performed to retrieve data of cardiovascular risk monitoring and changes in cardiometabolic medication prescriptions from 6 months after the SALINE study visit of the participant.

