### **12.3 Benefits and risk assessment, group relatedness**

Participation in the study is on a free-will base. Screening measurements are non-invasive and therefore no risks are associated with participation. The point of care measurements of HbA1c and creatinine are performed using a minimal invasive finger prick test. An indirect benefit could be that elevated albuminuria could be detected earlier because of the screening, and thus comes with health benefits. Another indirect benefit is that the medication is checked and compared to the most recent GP guidelines and on the GPs discretion be optimized if needed.

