### **13.3 Storage of personal data**

The handling of personal data will proceed confidentially. The pharmacy and general practitioner are offered the opportunity to use an ISO-certified post order company specialized in security for sending out the invitations. The data of eligible subjects will be handled in the secure and specialized environment of the post order company and will be destroyed after 21 days. Subjects receive a unique study identification number. GPRI has no access to the data of eligible subjects who will be invited. Only when subjects have signed the informed consent and have provided data by returning the completed questionnaire, GPRI receives pseudonymized patient data because the IC and questionnaire are marked by the identification number. During the analysis phase, all data provided by patients that signed the informed consent form are used pseudonymized. The identification number is not linked to the participant's personal information. A subject identification code list will be used to link the data to a participant, the key to the code will be safeguarded by the coordinating investigator. The de-identification process will only be used to contact the participant or his/her general practitioner if they have given consent.

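### Phase 3 is defined inconsistently in sections 4.3, 9.1.2 and 9.3, and the section 4.3 comparison with self-selected non-participants is biased as written

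*Protocol*

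**What the plan says.** **Comparison.** Section 4.3 plans an extraction "involving all patients who qualified for the SALINE study (thus both those who participate in SALINE and those who did not"). It looks at whether monitoring and prescriptions "have occurred in the 6 months following the albuminuria targeted screening", and will "compare those with participants who did not participate in SALINE". It mentions no earlier period for the non-participants.

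Section 9.1.2 (and the Summary) defines secondary endpoint 3 differently: "Change in frequency of cardiovascular risk factor monitoring, defined as the difference between the frequency" of monitoring "in participants 3 years before and 6 months after targeted albuminuria screening". Secondary endpoint 4 sets prescriptions in the 6 months after screening against the preceding three years. Neither endpoint mentions non-participants.

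**Start of follow-up.** Sections 4.3 and 9.1.2 count from targeted screening. Section 9.3, under Implementation of care, takes data "from 6 months after the SALINE study visit of the participant", and the Summary's study methods also count from the visit. Under section 4.2 only subjects with confirmed elevated albuminuria are invited to that visit.

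**Selection and adjustment.** Section 12.3 states: "Participation in the study is on a free-will base". Section 11 foresees systematic response bias, but limits post-stratification and weighting to the prevalence estimates. The monitoring and treatment outcomes are summarised as counts and proportions with confidence intervals.

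**Data access.** Section 13.3 states: "GPRI has no access to the data of eligible subjects who will be invited". GPRI receives pseudonymised data once consent and questionnaire are returned. Section 11 has practices supply aggregated data on the whole eligible population, but Table 2 lists characteristics only, with no monitoring or prescribing outcomes.

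**The concern.** Secondary objectives 3 and 4 have two competing definitions. One is a contrast between groups after screening. The other is a change over time, for endpoint 3 explicitly within participants. They answer different questions and can give opposite answers from the same data.

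The section 4.3 contrast has a bias that more data will not remove. People who return a urine kit, a consent form and a questionnaire may well have had more checks and prescription reviews anyway. The 3-year look-back that would show this is planned for the endpoints but does not enter this contrast.

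The starting points also conflict. A participant with a normal result has no visit date. A non-participant has neither a visit date nor a screening date. The 6-month window is therefore undefined for the comparison group and ambiguous for participants.

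Finally, section 4.3 relies on data about people who did not consent, and section 13.3 on its face keeps such data from GPRI.

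At stake is whether the answers to secondary objectives 3 and 4 can be interpreted.

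**Working it through.** **1. Who has a visit date.** Inputs from section 5.4: at least 112 examined at the visit, 57 examined in the pilot, at least 6300 eligible.
- 112 / 6300 = 1.8%.
- If the 57 pilot visits come on top: (112 + 57) / 6300 = 169 / 6300 = 2.7%.
- So about 97% to 98% of the eligible, including every non-participant, have no visit date.

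The protocol states no response rate. Over an assumed range of 20% to 80%, the share of participants with a visit is 112 / (6300 × response): 112 / 1260 = 8.9% down to 112 / 5040 = 2.2%. With 169 visits it is 13.4% down to 3.4%.

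**2. Unequal windows in section 9.1.2.** Assume a constant rate r of checks per year (Poisson), so that care does not change. The expected count is 3r in 36 months and 0.5r in 6 months. The chance of at least one check is 1 − exp(−3r) and 1 − exp(−0.5r).

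| Assumed r per year | Count, 36 months | Count, 6 months | At least one, 36 months | At least one, 6 months |
|---|---|---|---|---|
| 0.5 | 1.5 | 0.25 | 78% | 22% |
| 1 | 3.0 | 0.5 | 95% | 39% |
| 2 | 6.0 | 1.0 | 100% (rounded) | 63% |

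Unless frequency is put on a per-year basis, unchanged care appears as a fall. Counts can be annualised. A proportion with at least one event cannot simply be rescaled and needs equal windows.

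**3. Selection in the section 4.3 contrast.** Assume no effect of screening and habitual 6-month monitoring of 50% in non-participants. Assume a two-sided 5% comparison of two proportions with independent subjects.

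| Assumed prior difference | Response 30% (1890 v 4410) | Response 50% (3150 v 3150) |
|---|---|---|
| 2 points (52% v 50%) | 0.31 | 0.35 |
| 5 points (55% v 50%) | 0.95 | 0.98 |

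The entries are the probability that the groups appear to differ. For the lower left cell: standard error = √(0.55×0.45/1890 + 0.50×0.50/4410) = 0.0137; 0.05/0.0137 − 1.96 = 1.69; probability about 0.95. Clustering within sites would lower these probabilities but would leave the bias as it is.

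**4. Size of a real signal in the same contrast.** Suppose the visit and the report to the GP raised monitoring by an assumed 20 points in those visited, with no change in other participants. The contrast over all participants then moves by 20 × 112 / (6300 × response): 1.8 points at 20% response and 0.4 points at 80%. With 169 visits it is 2.7 to 0.7 points. A prior difference of a few points would be as large or larger.

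**5. Data route.** Section 4.3 needs post-screening outcomes for non-participants. Section 13.3 gives GPRI individual data only after consent and a returned questionnaire. The aggregated route in section 11 covers the right people but, in Table 2, not these outcomes. No stated route supplies the comparator.

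**The case against.** Several defences have force.

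- **The plan is not limited to the period after screening.** A reader might infer from section 4.3 that no baseline is used at all. The documents do not support that: endpoints 3 and 4 contain a 3-year look-back. The fault is that the look-back is missing from the between-group comparison and that the two definitions differ.
- **The visit is not the only starting point.** Sections 4.3 and 9.1.2 and the Summary's endpoints count from targeted screening. What stands is a conflict between two starting points, neither of which non-participants have.
- **The comparator is not shown to be unobtainable.** The no-access sentence in section 13.3 sits in a description of the invitation mailing, consenting participants' data are available, and section 4.3 does not say that individual non-participant records go to GPRI. Practices could supply aggregated outcomes. What stands is that the protocol does not say so.
- **The objectives are descriptive.** Objectives 3 and 4 speak of assessing frequency and changes, and nothing expressly promises a causal effect. Yet section 4.3 sets out to determine whether care changes after participation and brings in a comparison group for it, so the contrast is likely to be read as an effect.
- **Models, tests and clustering may be in a SAP that is not shown.** This is accepted. Their absence from section 11 is not part of the point, which rests on what the protocol says and where its sections disagree.

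**Conclusion.** The point holds as an inconsistency in the definition of Phase 3 together with a biased contrast in section 4.3. It affects secondary objectives 3 and 4 only and should be corrected.

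From the protocol's own figures, about 1.8% of the eligible (2.7% if pilot visits are additional) would have the starting date used in section 9.3. From the stated windows, the look-back is six times as long as the follow-up (36 / 6), which matters unless rates are annualised.

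The size of the selection bias cannot be derived from the protocol. The 2- and 5-point differences, the 20-point signal, the event rates and the response rates are all assumptions that show how the comparison behaves. A participant versus non-participant difference may therefore reflect prior care use. The documents do not show that it would, or by how much.

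**What to change.** 1. **One comparison.** In sections 4.3, 9.1.2 and 11, state for secondary objectives 3 and 4: the change in annualised monitoring and prescription-change rates, from the look-back already planned (or a pre-window of equal length) to the 6 months after, in participants minus non-participants. Report it as an association, and also with the confirmed-elevated subgroup as the participant side. This removes stable prior differences in care use. It does not remove differences that change over time.
2. **One index date.** Use a date that everyone has, for example the invitation date, in sections 4.3, 9.1.2 and 9.3 and the Summary. The cost is that kit return, repeat tests and the visit then fall inside the 6 months, which shortens follow-up after the report to the GP. A before-after analysis counted from the visit should therefore be kept for visited subjects.
3. **One data route.** State that non-participant data come as aggregated counts per site and time window, split by participation status, so that sections 4.3 and 13.3 agree. The cost is an additional aggregated extraction beyond Table 2, and limited scope for covariate adjustment.

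Otherwise the change is one of wording.
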